To reduce the mortality rate of ICU survivors, it is important to identify the group of patients who have a higher probability of death in the year following ICU discharge and to recognize the adjustable factors associated with mortality. Few data have been published regarding the long-term outcome of ICU patients, and most importantly, there are no recommendations for the long-term management of these patients, only experts opinion have been published [9, 10]. Some studies have demonstrated that mortality rates among ICU survivors are higher compared to the general population [11–15] and that ICU stay impact on patients’ quality of life [16]. Moreover, other studies [14, 15] found that this over-risk of mortality rates is sustained over time persisting after 5 or 15 years of follow-up. Three studies [11–13] reported a worse survival rate for the ICU patients than that for the age-matched control population in the first year after ICU discharge, they also observed that after 2 to 4 years, the survival curves of the two groups became parallel.

Table 2 describes the 15 largest studies from the last 30 years, investigating the one-year outcome of ICU patients and their associated risk factors [11, 13, 15, 17–28]. Using these 15 studies, the pooled estimate of post-ICU one-year mortality rate was 18.8 % (95 % confidence interval: 15.1 – 22.5 %), and the corresponding overall mortality (ICU + post-ICU one-year mortality) was 33.4 % (95 % CI: 27.0 – 39.9 %). However, only six papers out of fifteen had a prospective and multicenter study design (most were post-hoc analyses of prospectively collected data) [11, 19, 20, 23–25]. As expected older age was always associated with long-term mortality, along with APACHE score at admission (or within the first 24 h of the ICU stay). Other factors associated with long-term mortality were the presence and type of comorbidities and the cause of ICU admission.

**Table 2 Tab2:** The 15 largest studies including consecutive ICU patients, reporting one-year outcome and published in the last 30 years

Name	Country	Study design	Recruitment period	Sample size	Age (years)	Sex (M %)	Severity score	ICU mortality	One-year mortality after ICU discharge	Overall mortality	Factors associated with one-year mortality
Zaren B, 1989 [12]	Sweden	O/P/S	1983	978	53.6	58	N/R	9.6 %	18.7 %	26.5 %	age, AC (cardiac arrest, MOF, neurological or CV disease), chronic condition (DM, CHF, cortisone medication)

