#### Secondary objectives

The secondary objectives of this study are: 1) to determine the incidence and the risk factors of cardiovascular morbidity and mortality in the year following an ICU stay; 2) to evaluate quality of life in the year following an ICU stay; 3) to assess the role of novel biomarkers in assessing long-term outcome after ICU discharge (Table 3).

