### Data collection and biological samples

For each patient included, an electronic case report form will be completed that documents relevant information about the ICU stay and the one-year follow-up period. At the time of inclusion, the following will be collected: demographics, data on past medical history, ICU admitting diagnosis, hemodynamic (non-invasive and invasive) and respiratory parameters, severity of disease classification systems (SAPS-II, SOFA, CAM-ICU, McCabe Classification and GCS) [50–54]; digital electrocardiogram (EKG), recorded with CarTouch (Cardionics S.A., Bruxelles, Belgium), a high-definition electrocardiograph provided with TeleTouch software for the automatic transfer of the EKG to the informatics system. Routine laboratory tests will be performed. In 9 ICUs, an echocardiogram will also be performed within a few hours of inclusion. During the first 3 days of each ICU stay, respiratory and cardiovascular parameters (including hemodynamic and EKG) will be recorded daily and subsequently twice a week; SOFA score will be performed the first 3 days after inclusion, and routine biomarkers will be measured according to physician practice. Renal replacement therapy, death and cause of death in ICU will be collected.

The following data will be collected at ICU discharge: clinical parameters, digital EKG and routine biological assessment, ICU length of stay, duration of mechanical ventilation, SOFA score, treatment and results of echocardiogram at discharge when performed.

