All patients included in the study population who survive to ICU discharge will be followed up for one additional year or until death, except for severely disabled subjects (Glasgow Outcome Scale < 4 at discharge). One-year outcome will be evaluated through data collection at 3, 6 and 12 months after ICU discharge. At those time points, patients will be contacted by telephone, and information about vital status (patient dead or alive), re-hospitalization, and cardiovascular morbidity will be recorded. For patients lost of follow-up, the vital status will eventually be checked through the national health services records when available. In addition, 4 follow-up questionnaires will be submitted to the study population: the Hospitalization Anxiety and Depression Scale (HADS) [55] and the Short Form-36 (SF-36) [56, 57] at discharge and at 3, 6, and 12 months after and the Impact of Event Scale-Revised (IES-R) [58] at 3, 6 and 12 months; a social questionnaire for assessing patients’ social environments (actual occupation, resumption of activity, level of income, marital status,…) will be submitted at 3 months after discharge.

A biological collection will be created with blood (3x10 ml in EDTA and aprotinin) and urine (10 ml) samples collected at two different time points: admission and discharge. The biological collection will allow for the measurement of novel biomarkers in a central laboratory. Table 3 lists the biomarkers with potential interest for the risk stratification of patient who survive an ICU stay.

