The primary analysis will be based on the research of the determinants of 1-year mortality of patients included in the FROG-ICU (i.e., ICU patients who needed mechanical ventilation for more than 24 h and/or treatment with a positive inotropic agent over 24 and who were discharged alive from the ICU) among clinical and biological variables and biomarkers of common interest (i.e., troponins, natriuretic peptides). The regression model used will be the logistic model. The log-linearity of the quantitative variables will be systematically evaluated, and, if appropriate, variable transformations will be performed. A selection model process will be performed using stepwise selection method. The selection process model will be further validated by bootstrap [61]. The existence of any collinearities will be observed, and a test of goodness of fit will be performed using the test and the van Cessie Houwelingen method [62]. Finally a cross-validation procedure will be performed. The measures of association will be provided, with odds ratios and confidence intervals at 95 %. An estimate of related risks will also be conducted. Finally, the overall incidence of 1-year mortality will be estimated at a confidence interval of 95 %.

As it is now recognized that highlighting the statistically significant association between new biomarkers and patient outcomes is not sufficient to demonstrate the interest of these biomarkers in terms of risk prediction [63–65]. We will use the proposed methodology of Pencina et al., which has been used in multiple articles of application. For each biomarker of interest, the net reclassification improvement (NRI) and integrated discrimination improvement (IDI) will be calculated, and comparisons between different biomarkers will be performed [64].

Regarding quality of life, a strategy similar to that outlined for the 1-year mortality analysis will be used to assess its impact and to highlight the predictors of impaired QoL at 6 months or 1 year. QoL will be estimated using the SF-36 score (ranging from 0 to 100) [66]. Altered QoL is considered when SF-36 is lower than 50. In addition, the value of the SF-36 measured in the FROG ICU study will be compared with the values that are typically found in healthy populations of the same age and sex. Interaction between quality of life and social life will be assessed by using information from the social questionnaire.

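### The supplementary SF-36 comparison uses healthy age- and sex-matched values, so it cannot separate ill health present before admission from change after the ICU stay

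*Protocol article*

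**What the plan says.** Quality of life is a secondary objective: "to evaluate quality of life in the year following an ICU stay" (Secondary objectives). The Statistical analysis section gives it two analyses. The main one is a within-cohort model, built like the mortality model, intended "to highlight the predictors of impaired QoL at 6 months or 1 year". The second is an additional external comparison, in which the SF-36 values measured in the study "will be compared with the values that are typically found in healthy populations of the same age and sex". No other external reference for SF-36 is named.

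Under Data collection and biological samples, the SF-36 is given "at discharge and at 3, 6, and 12 months after". The items recorded at inclusion begin with "demographics, data on past medical history, ICU admitting diagnosis" and contain no quality-of-life instrument. The same section states that survivors with a Glasgow Outcome Scale below 4 at discharge are not followed up.

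The Background recognises prior illness as relevant in ICU populations: "Other factors associated with long-term mortality were the presence and type of comorbidities and the cause of ICU admission".

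**The concern.** A healthy reference leaves people with chronic disease out of one side of the comparison only. The eligibility criteria (Participants) select on ventilation or inotropic support and do not exclude chronic cardiac, respiratory or renal disease. A survivor with long-standing heart failure who returns exactly to the earlier state would still fall below the healthy value for the same age and sex.

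The comparison therefore shows how far survivors are from healthy people. It does not show how much of that distance arose after the ICU stay. This matters for a study whose secondary objective concerns the year after ICU, because a gap reported without qualification invites the reader to take it as a consequence of the stay.

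**Working it through.** The plan states no expected SF-36 difference, standard deviation or sample size for this comparison, so there is no figure of its own to reproduce. The check has three parts: what the comparison can identify, an illustration of size, and what a change of reference would remove.

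**1. What can be identified.** For the patients measured, let H be the healthy reference value, B their mean SF-36 before the ICU stay, and F their mean at follow-up. Then

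H − F = (H − B) + (B − F).

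- H comes from outside values matched on age and sex (Statistical analysis).
- F is measured at discharge and at 3, 6 and 12 months (Data collection and biological samples).
- B is never measured. The discharge score comes after the critical illness and cannot stand in for it.

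Only the sum is observed. The first term, H − B, is the deficit present before admission. It is above zero whenever some patients had earlier disease that lowers SF-36.

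The plan collects "data on past medical history", which could be used to split the comparison, but the text does not say that the comparison uses it.

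**2. Illustration of size, on assumed inputs.** Let p be the share of survivors with chronic disease before admission and d the mean SF-36 decrement from that disease against healthy peers. Neither is given in the documents. With no change at all after the ICU stay, the apparent deficit is p × d:

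| p (assumed) | d = 5 points | d = 10 points | d = 15 points |
|---|---|---|---|
| 30% | 1.5 | 3.0 | 4.5 |
| 50% | 2.5 | 5.0 | 7.5 |
| 70% | 3.5 | 7.0 | 10.5 |

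The range is 1.5 to 10.5 points. It shows that the component need not be trivial; it does not estimate it.

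**3. What general-population norms would remove.** If a share q of general-population peers has chronic disease with the same decrement, the remaining prior deficit is (p − q) × d. With assumed p = 60%, q = 30% and d = 10:

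- against healthy values: 0.60 × 10 = 6 points;
- against general-population norms: (0.60 − 0.30) × 10 = 3 points.

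In this example the change removes 3 of the 6 points and leaves 3. It reduces the problem without solving it, so separate presentation by comorbidity is also needed.

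**The case against.** The strongest reply is that the plan makes no causal claim. The objective is descriptive, and the analysis text says only that values will be compared. A reader might infer from the Background phrase "ICU stay impact on patients’ quality of life" that the gap will be attributed to the stay, but that phrase summarises earlier published work and is not this study's planned inference. This stands: the fault lies in what the comparison can show, not in a stated conclusion.

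Second, the comparison is an add-on. The main quality-of-life analysis is the within-cohort predictor model, which past medical history can enter. This also stands and limits the severity, but adjustment in that model does not alter the comparison with outside values.

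Third, no reference table is named, and the wording may loosely mean published population values. A condensed article may leave the choice of table to the full protocol. It is still the article's text that specifies healthy populations; if general-population values are meant, the sentence should say so.

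Fourth, distance from healthy peers is a legitimate descriptive question. That is true, provided the result is labelled as such.

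A reader might also see a contradiction with the Background, where survival is set against the general population and age-matched controls. Those were the controls of earlier mortality studies and do not commit this study to any quality-of-life reference.

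**Conclusion.** The point holds in limited form. With a healthy reference matched on age and sex alone and no pre-ICU SF-36, the comorbidity part of the gap exists before the ICU stay and the comparison cannot separate it from change afterwards. This requires only that some survivors had prior disease that lowers SF-36.

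Two stronger readings are not supported:

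- **A known size.** The 1.5 to 10.5 points rest wholly on assumed prevalence and decrement; the documents supply neither.
- **A net overstatement of the deficit.** The direction is fixed for the comorbidity component only. Severely disabled survivors are not followed, and SF-36 is available only from those alive and responding. Both may raise the observed scores and so narrow the gap. The net direction is undetermined.

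Severity is minor to moderate. The comparison is secondary and supplementary, and the primary mortality analysis does not depend on it.

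**What to change.** Amend the quality-of-life paragraph of the Statistical analysis section in three ways:

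1. Replace the healthy reference with age- and sex-matched general-population SF-36 norms, which include people with chronic illness. State that this reduces the prior deficit but does not remove it.
2. Present the comparison separately for patients with and without major comorbidity, defined in advance from the past medical history already collected at inclusion.
3. Report the gap as a descriptive difference from norms among the survivors measured, not as an effect of the ICU stay, and give the reason: no SF-36 was taken before admission.

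The cost is a change of wording and of reference table, with no new patient data. The reported gap is likely to be smaller, and precision within each comorbidity stratum will be lower than in the whole cohort.

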## Discussion

Very limited information is currently available concerning the risk factors for long-term survival after a stay in the ICU. Some studies have investigated the long-term prognosis of ICU patients [11, 13, 15, 17–28], but only a few of them have been properly designed to achieve this result, in a prospective, multicenter manner and using a large number of patients [11, 19, 20, 23–25]. Few studies have evaluated biological parameters [25–27] as factors associated with long-term mortality, and only one study has correlated the patient’s condition at discharge with the long-term risk of death [27]. Consequently, at the moment, there are neither guidelines nor recommendations to assist clinicians in providing optimal patient management after ICU.

Accordingly, FROG-ICU is an innovative study that reflects the endeavor of many ICU physicians to assess the incidence of all-cause mortality in the year after ICU discharge and to identify the factors associated with this mortality. The strengths of the present study are listed in Table 4: first is the study design because FROG-ICU is a large observational, prospective and multicenter cohort study; second, the evaluation of each patient is performed through a comprehensive clinical assessment, instrumental tests (electrocardiogram, echocardiogram) and biological parameters; finally, all of the data are collected at admission, during the stay and at discharge.

**Table 4 Tab4:** Strengths of the present study

Strengths of FROG-ICU study	
Study design	Observational, non-interventional, prospective and multicenter cohort study
Methods for the evaluation of the patient	Complete clinical assessment, instrumental tests (electrocardiogram, echocardiogram), biological parameters and routine biomarkers during ICU stay
Constitution of a biobank	For each patient, plasma and urine will be collected. For ICU-survivor, urine and plasma at discharge will also be collected
Repeated evaluations of the patient	At admission, during the ICU stay, at discharge and during one year

Preliminary studies suggest that pre-discharge therapy, especially the oral administration of beta-blockers, may improve the survival after an ICU stay [48, 49]. This would be confirm or not using the FROG-ICU data notably by using causal inference approaches. Moreover all of these findings favor developing a clinical trial with inclusion criteria and number of patients to be recruited based on the present study, with the main purpose of decreasing long-term all-cause and particularly cardiovascular morbidity and mortality after ICU discharge.

To sum up, FROG-ICU has been designed to better understand long term outcome after ICU discharge as well as risk factors for all-cause and cardiovascular morbidity and associated mortality. Because it is a large prospective multicenter study that collects clinical, biological and focused cardiovascular biomarkers, FROG ICU will allow to perform a risk stratification of ICU survivors as to recognize the subset of patients who may benefit from an early intervention to allow decreased cardiovascular morbidity and related mortality. Should the cardiovascular risks be identified here and validated in a sub-cohort, a randomized controlled trial using the results of this risk stratification will be in order to demonstrate survival benefits from a pre- and post-discharge multifaceted intervention that will include close cardiovascular monitoring and oral cardio-vascular therapies.
